#### Secondary outcome analysis

The secondary outcomes will be analysed as detailed in table 3. Binary outcomes will be analysed using logistic regression and continuous variables with linear regression. The sensitivity and specificity for referable DR of the AI system and the Tanzanian ophthalmology residents will be reported by arm and for all participants.

**Table 3 T3:** Secondary outcome measures and analyses

Secondary outcome measure	Analysis details
Proportion of persons who attend the central ophthalmology clinic within 8 weeks of screening out of all those referred	We will measure this outcome, by trial arm, in the same manner as our primary outcome measure. This will be by logistic regression with attendance at 8 weeks the binary outcome and trial arm as the exposure. However, the denominator for this outcome measure will be all persons referred in each trial arm, in contrast to only persons with true referable DR in our primary outcome analysis.
Sensitivity and specificity for grading referable DR	All retinal images collected in the study will be graded by the AI system, the Tanzanian ophthalmology residents and the UK-certified graders (reference standard). This will enable us to calculate the sensitivity and specificity of both the AI system and the local Tanzanian ophthalmologists for grading referable DR, relative to the reference standard.
False positive cases attending the central ophthalmology clinic	The number of false positive cases attending the central ophthalmology clinic will be compared between trial arms by logistic regression, with false positive cases attending the ophthalmology clinic as the outcome measure and trial arm as the exposure.
Number of patients receiving treatment after referral	The study is not powered to detect a difference in treatment uptake but we will undertake an exploratory analysis using logistic regression to compare treatment uptake between the trial arms for those participants who attend the ophthalmology clinic and who are recommended treatment.
Number of gradable versus ungradable retinal images	The number of images deemed ungradable will be compared between trials arms by logistic regression with gradable/ungradable retinal image as the outcome and trial arm as the exposure.
Time to presentation at hospital	The time to presentation at hospital will be compared between trial arms for all those referred to the central ophthalmology clinic after screening. We will use Cox proportional hazards regression with trial arm as the primary predictor. Survival curves using Kaplan-Meier will be plotted for both trial arms to represent the time to presentation at hospital.
Incremental cost per QALY gained	The economic evaluation aims to assess the cost-effectiveness of an AI-supported screening model compared with standard of care model. Cost-effectiveness results will be expressed in terms of incremental cost-effectiveness ratios (ICERs) per QALY gained. A Markov model will be built to undertake the analysis. Both deterministic and probabilistic sensitivity analyses will be performed to test the robustness of the model. Uncertainty in the parameters in the model will be reflected using probability distributions and the overall decision uncertainty will be presented using cost-effectiveness acceptability curves.
Acceptability, appropriateness and fidelity of AI screening	A process evaluation will be embedded within the trial and will be undertaken using the Medical Research Council guidance.^24^ Using semistructured interviews with participants, screening team staff, ophthalmologists and Ministry of Health officials we will assess the acceptability of AI-supported DR screening from different perspectives (patients, staff, policy makers). These qualitative data will be analysed using NVivo according to a condensation of meaning analysis and units of meaning will be coded into central themes. The fidelity of AI-supported screening will be assessed during the trial by random spot checks evaluating the delivery of the intervention. Staff members will be asked to keep a log of any difficulties encountered while delivering the intervention, thereby highlighting implementation barriers and challenges.

AI, artificial intelligence; DR, diabetic retinopathy; QALY, quality-adjusted life year.

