### Objectives

The primary objective of this study is to determine if AI-supported DR screening can increase the proportion of people with true referable DR who attend the central ophthalmology clinic following referral after screening for assessment and treatment. The secondary objectives are: (1) to compare prospective programmatic sensitivity and specificity of AI-supported and standard DR screening for the detection of referable DR and (2) to determine the impact of AI-supported screening on other key screening programme indicators including false positive referrals, treatment uptake, gradable versus ungradable image capture and to undertake an economic evaluation.

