### Follow-up assessment

All participants screened in the trial will be tracked to determine whether or not they attend the central ophthalmology clinic. Any participant recommended to attend a follow-up appointment who has not done so within 8 weeks of screening will be considered a non-attender. A follow-up period of less than 8 weeks could bias in favour of the intervention as some participants in the standard of care arm may not receive their screening result until 3–4 weeks after screening. As attendance at the central ophthalmology clinic beyond 8 weeks becomes increasingly less attributable to the DR screening result, it is our view that attendance within 8 weeks of screening is most appropriate.

For participants who attend the ophthalmology clinic we will document what, if any, treatment they are recommended and whether they commence the recommended treatment.

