#### Secondary outcome measures

The proportion of persons who attend the central ophthalmology clinic within 8 weeks of screening out of all those referred, by trial arm.Sensitivity and specificity for grading referable DR.Number of false positive cases attending the central ophthalmology clinic, by trial arm.Number of patients receiving treatment after referral, by trial arm.Number of gradable versus ungradable retinal images.Time to presentation at hospital.Incremental cost per quality-adjusted life year gained.Acceptability, appropriateness and fidelity of AI screening.

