### Sample size considerations

This study is powered to test the hypothesis that AI-supported DR screening increases the proportion of persons with true referable DR who attend the central ophthalmology clinic following referral after screening.

Our prior evaluation of the DR screening programme showed that the rate of follow-up for persons referred from screening to the ophthalmology clinic was 42%.^8^ Using this value, and in discussion with our partners in Tanzania, it was agreed that a 33% increase in compliance with follow-up recommendations would be a significant and programmatically meaningful improvement to the service.

Assuming that 22.5% of persons screened have true referable DR, with 1182 persons screened per trial arm (2364 persons in total), and therefore 266 persons with true referable DR in each arm, we would have a 90% power to detect a 33% uplift (from 42% to 56%) in attendance at the ophthalmology clinic for those persons with true referable DR.

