### Analysis plan

The analysis will be by intention to treat and all participant data will be analysed according to their randomisation allocation. However, not all participants randomised will be included in all analyses. For example, our primary outcome analysis includes only those persons with true referable DR as defined by the reference standard gradings.

The data will be analysed and reported according to the Consolidated Standards of Reporting Trials (CONSORT) AI extension guidelines for reporting RCTs.^18^ These guidelines are based on the CONSORT 2010 guidelines and have been adapted to produce a set of recommendations for clinical trials evaluating interventions with an AI component.

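### Treatment uptake is compared between arms only among attenders recommended treatment, a group shaped by the primary outcome, so the odds ratio cannot show the pathway's effect on how many people are treated

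*Protocol article*

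**What the plan says.** The Objectives section of the protocol article includes the aim "to determine the impact of AI-supported screening on other key screening programme indicators including false positive referrals, treatment uptake". The matching entry under Secondary outcome measures is "Number of patients receiving treatment after referral, by trial arm".

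The analysis is fixed in Table 3 (Secondary outcome analysis). Its purpose there is given as: "compare treatment uptake between the trial arms for those participants who attend the ophthalmology clinic and who are recommended treatment". The same row also gives the method and the status of the analysis: "The study is not powered to detect a difference in treatment uptake but we will undertake an exploratory analysis using logistic regression". No treatment comparison is stated with all randomised, all referred or all true referable participants as the denominator.

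Follow-up assessment says that every screened participant is tracked for attendance, and that treatment is recorded for those who attend: "For participants who attend the ophthalmology clinic we will document what, if any, treatment they are recommended and whether they commence the recommended treatment". For the primary outcome, the sections on loss to follow-up and on the adjusted analysis keep people who do not come in the analysis as non-attenders. No matching rule is given for treatment.

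**The concern.** The trial is powered on the hypothesis that "AI-supported DR screening increases the proportion of persons with true referable DR who attend the central ophthalmology clinic following referral after screening". Table 3 then restricts the treatment comparison to people who attended and were recommended treatment. If the intervention works as hypothesised, the AI arm contributes attenders who would have stayed away under standard care. Two things follow.

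- The comparison is no longer between randomised groups. The additional AI-arm attenders may differ from the others in their readiness to accept treatment.
- The gain in treatment that comes through higher attendance is removed by design. The OR describes acceptance of treatment once a person is in the clinic and recommended it. The objective and the listed outcome ask how many people end up treated under each pathway.

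At stake is the reading of the treatment result: an OR at or below 1 could stand beside a larger number treated in the AI arm.

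**Working it through.** **The plan's own figure.** Sample size considerations gives 1182 screened per arm, 22.5% with true referable DR, attendance 42% v 56% and 90% power. A two-sided alpha of 0.05 is assumed, in line with the 95% CI in the primary analysis.

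- 1182 × 0.225 = 265.95, so 266 per arm.
- n = [1.96 × √(2 × 0.49 × 0.51) + 1.2816 × √(0.42 × 0.58 + 0.56 × 0.44)]² / 0.14² = 266. Power at 266 is 0.900. The figure reproduces.

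**Inputs not in the document.** r = share of attenders recommended treatment; u = uptake among those recommended. Both are assumed and varied. Only true referable cases are counted, and the 42% who would attend under standard care are taken to be contained in the 56%.

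**Attenders.** 266 × 0.42 = 111.7 and 266 × 0.56 = 149.0.

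**Case 1: r and u equal in both arms.** Treated = 266 × attendance × r × u. With r = 0.5 and u = 0.8:

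- Standard care: 266 × 0.42 × 0.5 × 0.8 = 44.7 (16.8% of 266).
- AI: 266 × 0.56 × 0.5 × 0.8 = 59.6 (22.4% of 266).
- Ratio treated = 0.56 / 0.42 = 1.33.
- Planned OR = (0.8/0.2) / (0.8/0.2) = 1.00.

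The planned OR is 1.00 and the ratio treated is 1.33 for every r and u. Over r = 0.2 to 0.7 and u = 0.5 to 0.9, the numbers treated run from 11 v 15 to 70 v 94. With all 266 as denominator the OR is 1.35 to 1.52, with power of about 11% to 60%.

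**Case 2: only the additional AI-arm attenders have a different uptake, v.** AI-arm uptake = (0.42u + 0.14v) / 0.56 = 0.75u + 0.25v. Ratio treated = (0.42u + 0.14v) / 0.42u = 1 + v/(3u). With r = 0.5 and u = 0.8:

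| v | AI-arm uptake | Planned OR | Treated, standard v AI | Ratio treated |
|---|---|---|---|---|
| 0.70 | 77.5% | (0.775/0.225)/4 = 0.86 | 45 v 58 | 1.29 |
| 0.50 | 72.5% | (0.725/0.275)/4 = 0.66 | 45 v 54 | 1.21 |
| 0.40 | 70.0% | (0.700/0.300)/4 = 0.58 | 45 v 52 | 1.17 |

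Under these assumptions the planned OR is below 1 whenever v < u, while more people are treated whenever v > 0. Over u = 0.7 to 0.9 and v = 0.3 to 0.6, the planned OR is 0.33 to 0.89 and the ratio treated is 1.11 to 1.29.

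**Precision.** In the v = 0.40 row, about 56 v 74 people are recommended treatment: 44.7 treated and 11.2 not, against 52.1 and 22.3. SE of the log OR = √(1/44.7 + 1/11.2 + 1/52.1 + 1/22.3) = 0.42, so the 95% CI for 0.58 is about 0.26 to 1.33.

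**The case against.** The strongest defence is that the plan does not oversell this analysis. Table 3 calls it exploratory and unpowered, and the list of strengths and limitations repeats that the trial is not powered for treatment uptake. The listed outcome is a count by arm, and with 1:1 allocation those counts would show the larger number treated beside the OR. All of this stands and limits the harm. It does not remove the problem: low power concerns precision, whereas the restriction decides who is compared. A larger trial would estimate the same conditional quantity more precisely.

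Three stronger readings are tempting and are not supported.

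- A reader might infer that the planned OR would read as evidence of harm. With about 56 v 74 people, even an OR of 0.58 has an interval well above 1, and reaching it takes uptake of 40% among the additional attenders, half the assumed 80%. With 70% among them the OR is 0.86.
- A reader might infer that the plan mislabels this as an intention-to-treat analysis, because the Analysis plan says "The analysis will be by intention to treat and all participant data will be analysed according to their randomisation allocation". The next sentence there says openly that some analyses will not include every randomised participant.
- A reader might extend the criticism to attendance among those referred, where "the denominator for this outcome measure will be all persons referred in each trial arm". That measure is openly set apart from the primary outcome and is the programme indicator behind the 42% baseline. Keeping it is a reasonable choice.

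**Conclusion.** The point holds for the treatment-uptake row of Table 3. The only between-arm treatment analysis that the article fixes is conditional on attendance, so it is not a randomised comparison and answers neither the listed outcome nor the stated objective. With equal recommendation and uptake rates, it returns 1.00 while a third more people are treated. With lower uptake among the additional attenders, it falls below 1 while more are treated, though imprecisely.

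The OR of 1.00 against a ratio of 1.33 in the equal-rates case needs only the plan's attendance figures. The article presents the 33% uplift as the programmatically meaningful difference used for power, not as a forecast. The counts and the ORs below 1 rest on assumed recommendation and uptake rates, and on the additional attenders having the same recommendation rate as the others. The weight is moderate: this is one secondary, exploratory outcome. The primary outcome is not affected, because its denominator comes from reference grading masked to the other gradings.

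**What to change.** Reword the treatment row of Table 3 as follows.

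- The between-arm comparison is started recommended treatment at the central clinic, yes/no, in all randomised participants by arm, with non-attenders counted as not treated there. This denominator also keeps people referred and treated who are not positive on the reference standard, as the listed outcome implies.
- Repeat it in all participants with true referable DR, the primary denominator.
- Report uptake among attenders recommended treatment as a descriptive percentage by arm, without a between-arm test.
- Keep the statement that the analysis is exploratory and unpowered.

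The cost is a wording change. Attendance is already tracked for everyone screened and treatment is already recorded for attenders. Counting non-attenders as not treated mirrors the rule for the primary outcome. The article gives the trial as recruiting, with analysis only at the end, so the change can be specified in advance if that is still the case.

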**Methods and analysis:**

We will test the hypothesis that AI-supported DR screening increases the proportion of persons with true referable DR who attend the central ophthalmology clinic following referral after screening in a single-masked, parallel group, individually randomised controlled trial. Participants (2364) will be randomised (1:1 ratio) to either AI-supported or the standard of care DR screening pathway. Participants allocated to the AI-supported screening pathway will receive their result followed by point-of-screening counselling immediately after retinal image capture. Participants in the standard of care arm will receive their result and counselling by phone once the retinal images have been graded in the usual way (typically after 2–4 weeks). The primary outcome is the proportion of persons with true referable DR attending the central ophthalmology clinic within 8 weeks of screening. Secondary outcomes, by trial arm, include the proportion of persons attending the central ophthalmology clinic out of all those referred, sensitivity and specificity, number of false positive referrals, acceptability and fidelity of AI-supported screening.

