### Clinical assessment

Following assessment of eligibility criteria and the informed consent process, the participant will proceed with the clinical assessment (table 2). In summary, it will include a basic demographic and clinical history, visual acuity testing, blood sugar and blood pressure measurement, followed by fundus photography.

**Table 2 T2:** Demographic and clinical data

Assessment	Details
Demographic history	Sex, age, education level, occupation, self-reported tribe/ethnicity, health insurance status.
Clinical history	Type of diabetes, duration of diabetes, current diabetes treatment (diet, medications, insulin), smoking history, alcohol consumption, known hypertension, any known diabetes complications, previous heart attack or stroke.
Visual acuity	Presenting best corrected VA. VA will be measured using a Tumbling-E logMAR chart with the PEEK VA smartphone application^20^ by a trained study team member, for each eye separately.
Blood pressure	BP will be measured using a calibrated A&D (A&D Instruments, Abingdon, UK) UA-651 BP monitor.^21^ Using the WHO STEPwise approach to NCD risk factor surveillance protocol,^22^ three measurements will be taken 1 min apart after the participant has rested for 5 min, with an average of the final two measurements recorded.
Random blood sugar	A random blood sugar measurement will be taken using a Contour Next Meter (Ascensia Diabetes Care, UK)^23^ and recorded in mmol/L.
Fundus photography	One drop of tropicamide 1% will be instilled into each eye separately. After 30 min (to allow adequate pupil dilation) a Topcon NW8 fundus camera will be used to capture two retinal photographs of each eye: one disc centred image and one macular centred image. The retinal images will be captured by a trained medical photographer.

BP, blood pressure; NCD, non-communicable disease; VA, visual acuity.

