### Randomisation

#### Randomisation sequence

A computer-generated randomisation list will be prepared by a statistician at London School of Hygiene & Tropical Medicine (LSHTM). The sequence will be in a 1:1 allocation ratio of standard DR screening to AI-supported DR screening, blocked with a random block size of 4–8.

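### Table 3 compares image gradability between arms by logistic regression on images, with no provision for the four images that each participant normally gives

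*Protocol article*

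**What the plan says.** The list under Secondary outcome measures names this outcome as "Number of gradable versus ungradable retinal images", and the registration summary in Table 4 repeats it in the same terms. Table 3, under Secondary outcome analysis, gives the method: "The number of images deemed ungradable will be compared between trials arms by logistic regression with gradable/ungradable retinal image as the outcome", with trial arm as the exposure. The text introducing that table sets the general rule: "Binary outcomes will be analysed using logistic regression and continuous variables with linear regression".

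Table 2, under Clinical assessment, describes the photography: the camera is used "to capture two retinal photographs of each eye: one disc centred image and one macular centred image". A participant with two photographed eyes therefore gives four images.

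The unit of randomisation is the person. The abstract says "Participants (2364) will be randomised (1:1 ratio) to either AI-supported or the standard of care DR screening pathway".

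The article does not mention clustering by participant or eye, robust standard errors, GEE or random effects, and does not reduce this outcome to one record per person.

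**The concern.** The unit named for the analysis (the image) is smaller than the unit randomised (the participant). Images of one person come from one sitting, one camera and one pair of eyes, so they can be expected to be gradable or ungradable together more often than chance would give. Logistic regression with its usual model-based variance counts each image as a separate piece of information. If the images of a person are positively correlated, the standard error is too small, the confidence interval too narrow and the p-value too low.

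At stake is the validity of the interval and test for one registered secondary outcome. The error would make an apparent difference in gradability between arms, in either direction, look better supported than it is. This has some programme relevance, because the article counts an ungradable image as a ground for referable status.

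**Working it through.** **The plan's own figure.** The article states no number for the gradability outcome. Its only calculation concerns the primary outcome: "with 1182 persons screened per trial arm (2364 persons in total), and therefore 266 persons with true referable DR in each arm", for 90% power to detect 42% versus 56%. This reproduces. 1,182 × 0.225 = 265.95, and a two-sided 5% comparison of two proportions with pooled variance and no continuity correction needs 266 per arm and has power 0.9002. That outcome has one record per person, so nothing below touches it.

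**Inputs for gradability.**
- Images per participant, m = 2 eyes × 2 photographs = 4 (Table 2).
- Participants per arm = 1,182 (Sample size considerations), so images per arm = 1,182 × 4 = 4,728.
- Test level: two-sided 5%, assumed, in line with the 95% CI that the article plans for the primary outcome.
- Within-person correlation (ICC): not in the article; assumed at 0.1, 0.3, 0.5 and 0.7.

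**Formulas.** Design effect DE = 1 + (m − 1) × ICC. Ratio of naive to true standard error = 1/√DE. True size of the nominal 5% test = 2 × [1 − Φ(1.96/√DE)]. Effective number of images per arm = 4,728/DE.

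**Results for m = 4.**

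| ICC (assumed) | DE | Naive SE / true SE | Effective images per arm | True size |
|---|---|---|---|---|
| 0.1 | 1 + 3 × 0.1 = 1.3 | 0.877 | 3,637 | 8.6% |
| 0.3 | 1 + 3 × 0.3 = 1.9 | 0.725 | 2,488 | 15.5% |
| 0.5 | 1 + 3 × 0.5 = 2.5 | 0.632 | 1,891 | 21.5% |
| 0.7 | 1 + 3 × 0.7 = 3.1 | 0.568 | 1,525 | 26.6% |

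**If only two correlated records per person entered** (for example, one per eye), DE = 1 + ICC and the true size would be 6.2%, 8.6%, 11.0% and 13.3% over the same four values.

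**Simulation check.** Beta-binomial data were generated under no arm difference, with 1,182 persons per arm, four images each, assumed ungradable rates of 5%, 10% and 20%, and 4,000 runs per setting. Rejection rates at nominal 5% were:
- logistic regression on images with model-based variance: 8.6–8.9% (ICC 0.1), 15.5–15.9% (0.3), 20.4–22.7% (0.5), 26.0–26.5% (0.7);
- the same odds ratio with standard errors clustered on participant: 4.5–5.4% across all settings;
- one record per person (any ungradable image): 4.2–6.0% across all settings.

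The simulation agrees with the formula, and either remedy restores the nominal level.

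**The case against.** There are four serious points on the other side.

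**The variance estimator is not stated.** Table 3 says logistic regression; it does not say that images will be treated as independent. A logistic model fitted by GEE or with participant-clustered errors would fit the sentence, and a condensed article may leave that to an analysis plan that is not shown. This stands in part. A reader might infer that the trial will certainly report a wrong interval and p-value, and the article does not support that. It does fix both the image as the outcome record and the model, though, and that pair followed as written does not suit the design. The point is therefore more than a missing detail.

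**The unit may be the person.** Under Grading of retinal photographs, an ungradable image is one of the criteria that classify a participant as having true referable DR. The Interim analysis section likewise moves from images to the participant's referral status. The other binary arm comparisons in Table 3 concern persons or cases. If one record per person was meant, there is no error. This reading is open, but Table 3, the outcome list and the registration summary all speak of images.

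**The size is unknown.** No correlation is given, and at a low value the inflation is modest (8.6% at 0.1). This stands: only the direction is certain, and only given positive correlation.

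**The consequence is limited.** A reader might extend the problem to the primary result or the power. The primary analysis uses one record per person and the sample size reproduces, so neither is affected. Nor is the odds ratio for gradability biased when every person gives the same number of images; only its stated precision is at issue.

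**Conclusion.** The point holds in a limited form. Taken literally, the Table 3 analysis of gradability ignores that each randomised participant normally gives four images, and it understates the standard error for any positive within-person correlation. Under the assumed range of 0.1 to 0.7, the naive standard error is 0.88 down to 0.57 of the true one, and a nominal 5% test rejects a true null in about 9% to 27% of trials.

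This rests on three assumptions: four images per person, a model-based variance, and a correlation that the article does not supply. If one record per person was intended, the inflation is nil. The finding is confined to this one secondary outcome, and it is a matter to correct or clarify before analysis rather than a threat to the trial's main conclusion.

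**What to change.** Keep the image as the unit, as the outcome list and the registration summary name it. Add to the Table 3 row that the logistic regression will be fitted by GEE, or with cluster-robust standard errors, with participant as the cluster. With equal numbers of images per person, cluster-robust errors leave the odds ratio as it is and correct only its precision.

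If a per-person outcome was meant, say so in Table 3 and define it, for example as any ungradable image. This is a larger change than it looks: it alters the outcome and the odds ratio as well as the interval, and the outcome list and registration wording would have to be brought into line.

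The cost of the first option is a short addition to one table row and a wider confidence interval, by a factor of √DE: 1.14, 1.38, 1.58 or 1.76 at the four assumed correlations. Neither option needs new data.

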### Grading of retinal photographs

All retinal images captured in the trial will be graded by (1) the Tanzanian ophthalmology residents, (2) the AI system and (3) UK-certified graders. This will enable comparison of the performance of the AI system versus Tanzanian ophthalmology residents and against a reference standard (UK-certified graders). All graders will be masked to the other DR gradings.

For the reference standard gradings, the UK-certified graders will undertake feature-based grading and the retinal images will be labelled using a software program (OptoMize, NEC Software Solutions, UK) commonly used in the English National Screening Programme. All images will be labelled by two experienced graders from the English National Screening Programme. The graders will only have access to anonymised retinal images with no patient metadata. Any disagreements will be adjudicated by a third senior grader. All graders involved are subject to the English Diabetic Eye Screening quality assurance process.

Participants noted to have any of the following after grading by the UK-certified graders will be defined as having true referable DR: preproliferative, proliferative DR, referable maculopathy or an ungradable retinal image. Referable maculopathy is defined as the presence of hard exudates or blot haemorrhage within 1 disc diameter of the fovea (centre of the retina) or a circinate or group of exudates within the macula. This definition of referable DR and maculopathy follows the Tanzanian National Guidelines for the Management of DR (published by the Tanzanian Ministry of Health) which is the nationally approved standard of care for Tanzania.

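### Gradability is compared only between trial arms, by plain logistic regression on images, although AI and residents read every image and a paired, participant-clustered comparison would separate reader from capture

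*Protocol article*

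**What the plan says.** The secondary objective (Objectives) is the effect of AI-supported screening on programme indicators, among them "gradable versus ungradable image capture". The listed outcome (Secondary outcome measures) is "Number of gradable versus ungradable retinal images". For the analysis, Table 3 under Secondary outcome analysis states: "The number of images deemed ungradable will be compared between trials arms by logistic regression". The model's exposure is trial arm, and its outcome is whether an image could be graded. None of these places says whose judgement makes an image ungradable.

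Capture is described once, for everyone (Clinical assessment, Table 2): after the same drops for all, "a Topcon NW8 fundus camera will be used to capture two retinal photographs of each eye". The operator is named without any distinction by arm: "The retinal images will be captured by a trained medical photographer". No arm-specific capture or retake step appears.

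Reading is also common to both arms. The section Grading of retinal photographs makes this explicit in its opening sentence: "All retinal images captured in the trial will be graded by (1) the Tanzanian ophthalmology residents, (2) the AI system and (3) UK-certified graders". None of the readers sees another's result: "All graders will be masked to the other DR gradings". The UK graders see anonymised images without patient metadata. An image that they find ungradable counts as true referable DR.

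**The concern.** Two processes can change the number of ungradable images: how the picture was taken, and how strict the reader is. Trial arm as the only exposure does not separate them, and what the odds ratio means depends on a reader who is not named.

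- **One common reader for both arms.** The odds ratio can pick up only a difference in capture. Under the single written procedure none is expected, so the result would say little about AI reading.
- **Each arm's own reader (AI in one arm, residents in the other).** The odds ratio is a pathway contrast in which capture and reader threshold are combined. It is estimated on different people although both readers graded everyone, so precision is lost.

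In addition, the outcome is counted in images, four per participant, and the stated model makes no allowance for images of one person being alike.

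At stake are the interpretation and precision of one secondary outcome. The capture question also has a link to the primary analysis, because reference-ungradable images feed its denominator.

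**Working it through.** **The plan's own figures.** The article gives no rate, difference or power for gradability. Its only sample size is for the primary outcome, and it reproduces. For 42% v 56%, 90% power and two-sided 5% (assumed from the 95% CI), n = [1.96·√(2·0.49·0.51) + 1.2816·√(0.42·0.58 + 0.56·0.44)]² / 0.14² = 265.9, that is 266 per arm, and 1182 × 0.225 = 265.95. The present point does not touch it.

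**Inputs for gradability.** From the article: 1182 per arm, 2364 in total, and two photographs of each eye, so four per person. Assumed, at person level: ungradable rates p₁ (AI) and p₂ (residents), and the discordance d, the share of people on whom the two readers disagree.

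**Case 1, one common reader.** With identical capture the expected arm difference is 0, and a correctly specified test rejects at about its 5% level. This holds only as far as capture really is identical.

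**Case 2, each arm's own reader, against pairing.**

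- By arm: variance = [p₁(1−p₁) + p₂(1−p₂)] / 1182.
- Paired on everyone: variance = [d − (p₂−p₁)²] / 2364, which equals [p₁(1−p₁) + p₂(1−p₂) − 2·cov] / 2364.
- The ratio is therefore exactly 2 when the readers' calls are uncorrelated and above 2 when they are positively correlated, whatever the rates.

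With p₁ = 10% and p₂ = 15%:

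- By arm: √[(0.09 + 0.1275)/1182] = √(0.2175/1182) = 1.36 points.
- Paired, d = 9%: √[(0.09 − 0.0025)/2364] = 0.61 points; variance ratio 5.0.
- Paired, d = 15%: √[(0.15 − 0.0025)/2364] = 0.79 points; variance ratio 2.9.
- Uncorrelated readers: d = 0.10·0.85 + 0.15·0.90 = 22%, and the ratio is 2.0.

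Power at smaller assumed differences (two-sided 5%; normal approximations, McNemar for the paired test), at between-reader correlation 0, 0.3 and 0.5:

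| Assumed rates | By arm, 1182 v 1182 | Paired, 2364 (correlation 0 / 0.3 / 0.5) |
|---|---|---|
| 5% v 7% | 54% | 83% / 93% / 98% |
| 10% v 13% | 63% | 90% / 97% / 99.5% |
| 20% v 23% | 43% | 71% / 85% / 94% |

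**Clustering.** Arm is constant within a person. With four images per person and within-person correlation ρ, the variance of a by-arm image comparison is multiplied by 1 + (4−1)ρ, between 1 (ρ = 0) and 4 (ρ = 1). A model that treats images as independent can thus understate the standard error by up to a factor of √4 = 2. The documents give no ρ.

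**The case against.** The best defence is that the objective asks about the programme, not the readers. This is a pragmatic trial of a complex intervention, and a randomised comparison by arm estimates the effect of the pathway directly. If each arm's own reader is used, the mix of capture and reader threshold is that pathway effect. This stands: the contrast is unbiased. A reader who infers from the shared readings that the by-arm analysis is biased or invalid goes beyond the documents. What it lacks is precision and a separation of the two sources.

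A reader might also infer that the by-arm comparison is null by design. The article does not support that either. It does not say whether photography comes before or after the envelope is opened, nor that one photographer serves both arms. Screening staff are unmasked, and the AI result arrives while the participant is present. Effort or retakes could differ by arm. No such step is described, so this is a possibility only, but it is the reason to keep a by-arm comparison.

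Naming the reader, and perhaps the handling of clustering, can be left to a SAP that is not shown. As a missing detail alone, the unnamed reader would be no finding. What the article does fix is arm as the only contrast for this outcome. In the same section, sensitivity and specificity are calculated for each reader and reported by arm and for all participants.

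Finally, in the 10% v 15% example the by-arm test is already strong: z = 5/1.36 ≈ 3.7, power about 96%. The loss matters at smaller differences, such as those in the table.

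**Conclusion.** The point holds as one of efficiency and interpretation. The stated analysis yields either a capture comparison that says little about AI reading, or an unbiased pathway contrast that blends capture with reader threshold and has at least twice the variance of the paired alternative. The factor of two rests only on non-negative correlation between the readers. The larger ratios, 2.9 and 5.0 in the example, and all the powers rest on assumed rates and discordance at person level. Ignoring clustering could further make the by-arm intervals too narrow, by an amount that the documents do not allow one to calculate.

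Only a secondary outcome is affected. The link to the primary denominator might suggest that the primary analysis is wrong; nothing in the documents shows that capture differs by arm, so the link is a reason for a check and no more.

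**What to change.** Replace the gradability row of Table 3 with two analyses, each naming the reader and the unit (image, eye or person):

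- **(a) Reader effect.** Compare AI and resident ungradable calls on the same images from all participants by a paired method: GEE or mixed logistic regression with reader as the exposure and clustering on participant, or McNemar's test at person level.
- **(b) Capture difference.** Compare images ungradable by the masked UK reference grade between trial arms, by logistic regression clustered on participant. This measures any difference in capture by unmasked staff and checks that the reference-ungradable part of the primary denominator arose equally in both arms.

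The cost is a reworded table row. All three gradings are already planned for every image, so no new data and no change in sample size are needed.
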